## Assessments and Procedures

### Clinic visits

Visits to the clinic will be performed at Baseline (Visit 2, Day 0), Initial Safety Follow-up (Visit 3a-3c, Week 2/4/6) and at the Final Safety Follow-up (Visit 12, Week 48).

The Screening visit shall be held approximately 4 weeks after the transplantation procedure is completed.

### Informed consent

All subjects participating in the study will be required to be thoroughly informed of the study, given the opportunity to ask study-related questions to the Investigator at the site, and must be given sufficient time to review the patient information sheet. Following this procedure, all subjects willing to participate in the study will be asked to sign and date the informed consent form. The Investigator will also sign and date the form to corroborate that the subject has been thoroughly informed about the study. A photocopy of the signed form will be created by the site who will distribute the copy to the patient. The original informed consent is to be retained by the site.

### Review of inclusion/exclusion criteria

During the Screening Visit Investigator will perform a thorough review of the eligibility criteria for the study. The subject is required to fulfill all of the inclusion criteria and must not fulfill any of the exclusion criteria to be eligible for inclusion in the study. Patients who are considered eligible will also be re-reviewed with regard to eligibility at the Baseline Visit.

### Medical history and concomitant diseases

A review of the subject’s medical history and concomitant diseases will be performed at Screening and at Baseline by the Investigator asking the subject for any information and/or by the Investigator reviewing the patient file if this information is available. A complete review of the subject’s medical history and concomitant diseases will be undertaken by the Investigator to ensure that all inclusion and no exclusion criteria have been met. The Investigator may, with the consent of the subject, contact other physicians who may be or have been responsible for the medical care of the subject in order to establish relevant medical history.

Any medical history considered relevant for the study by the Investigator, including all items listed below, shall be reported. Any conditions which have not presented within the last 5 years shall not be reported. .

All currently active concomitant diseases, whether considered relevant for the study or not by the Investigator, must be reported. The duration of diagnosis of medical history and concomitant diseases should be noted.

In particular, the review should determine whether any of the following conditions are currently present or have been in the past:

Hypercalcemia and/or treated by Mimpara

### Concomitant medication

See Section 5.5, below.

### Physical examination

The physical evaluation will include a review of organ systems by the Investigator as per standard clinical practice.

### Vital signs

The following vital sign evaluations will be performed at various visits during the study and recorded:

- Blood pressure: Will be performed as seated (after at least 5 minutes of rest) systolic and diastolic blood pressure (in mmHg).

All new findings or changes to previous findings considered clinically significant are to be recorded in the medical journal

### Randomisation

After review and confirmation that all study eligibility criteria have been met, the Investigator will assign a randomisation number to the subject on the Baseline Visit.

Additional information on the randomization procedure is available in Section 5.4.

### Study drug administration.

Patients allocated to Paricalcitol will get a prescription of orally 2 ug once daily for the entire duration of the study, unless reduction to 1 ug once a day due to hypercalcamia.

Compliance will be monitored with counting of capsules and collection of blister packs.

### Efficacy evaluation methods

#### Proteinuria

Measured as albumin/creatinine ratio at baseline and after 12 months.

**Note:** Proteinuria (albumin/creatinine ratio) will be measured automatically for the Baseline (Visit 1, Day 0) and Final Safety Follow-up (Visit 4, Week 48).

#### Kidney biopsy

A kidney biopsy will be performed at the Baseline visit (and at the Final Safety Follow-up in order to evaluate the degree of fibrosis, according to IF/TA (interstitial fibrosis/tubular atrophy). Kidney biopsy will be performed by the department of radiology according standard technique and will be evaluated according to degree of IF/TA. One section of the biopsy will be utilized to perform assessment of markers of fibrosis.

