# TREATMENT PROCEDURES

## Overall Study Design

The study is to be performed as a randomized open intervention study. Patient eligibility for the trial will be assessed around 4 weeks after transplantation. If the patient is considered eligible by the Investigator, the patient will attend the Baseline visit (Visit 1, Day 0). At the Baseline visit, the patient will undergo the study-specific evaluations listed in Section 4.3 and will be randomized in a 1:1 ratio to either treatment with paricalcitol or no treatment based on a computer-based allocation sequence.

After the Baseline visit has been completed, the patient will be asked to return to the clinic for the Follow-up visits in the study. The initial Follow-up visits will be the Initial Safety Follow-up visits held every two weeks after the Baseline visit up to Week 6. During these visits to the clinic, blood samples will be taken from the patient for laboratory evaluations and new or changes to pre-existing adverse events will be recorded. After Week 6 up to the final Follow-up visit held at Week 48, the patients will be followed up as per standard clinical practice.

At Week 48 of the study, the patient will return to the clinic for the final Final Follow-up visit (Visit 12, Week 48). This visit will evaluate both efficacy and safety parameters, further listed and described in Section 4.3/Section and Section 4.2, respectively. Every effort will be made in order to follow-up and complete patient evaluation at these Follow-up visits. Patients who are withdrawn for any reason will also be evaluated according to the evaluation flow-chart if possible.

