**Protocol biopsies are routinely performed on all transplanted patients at week 6 and month 12.**

Two renal biopsies are mandatory in the study protocol. The first biopsy should be taken at the time of inclusion, the second at 12 months after transplantation, respectively. There will not be required to obtain extra biopsy due to participation in the trial.

Biopsies will be taken according to our center’s common routine.

The Banff standard regarding the presence of sufficient number of glomeruli and arteries will be used

The laboratory will stain their own according to local practice. In addition the slides will be stained for C4d. The routine biopsy for C4d will be utilized for expression of fibrosis markers.

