#### Expression of Fibrosis markers in graft biopsies

Graft fibrosis will be assessed by Banff criteria and by morphological techniques.

RNA expression of following fibrosis markers

Transforming growth factor beta (TGF-beta)

Osteopontin

Thrombospondins

Tenascins

Osteonectin/Sparcs

Periostin

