#### Pulse Wave Velocity

1. Arterial stiffness will be assessed by means of PWV measurements using “SphygmoCor™” (Atcor Medical, Sidney, Australia), a non-invasive technique with direct-contact pulse sensors (Covic et al., 2005). Pulse waveforms will be recorded simultaneously, obtained transcutaneously over the common carotid artery and femoral artery in the groin. The PWV will be calculated as the distance between recording sites measured over the surface of the body (L), divided by the time interval (t) between the feet of the flow waves (PWV = L/t). The value is averaged over 10 cardiac cycles (Asmar et al., 1995).

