## Randomisation

The randomisation scheme (in a 1.1 ratio) will be generated by CRO using a computerised procedure. A complete randomisation list containing details of all patient numbers and study group will be stored as essential documentation in the Trial Master File and at the study site (open study).

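### In this open trial nothing keeps the reader of the 12-month IF/TA grade, or to a lesser degree the pulse wave velocity operator, unaware of allocation, so these two secondary outcomes are open to assessment bias

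*Protocol*

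**What the plan says.** **Openness.** Overall Study Design in the protocol states: "The study is to be performed as a randomized open intervention study". Patients receive "either treatment with paricalcitol or no treatment based on a computer-based allocation sequence". Under Randomisation in the statistical section, the full list is "stored as essential documentation in the Trial Master File and at the study site (open study").

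**Fibrosis.** Under Kidney biopsy, the specimen "will be evaluated according to degree of IF/TA". The section on fibrosis markers adds: "Graft fibrosis will be assessed by Banff criteria and by morphological techniques". On handling, the biopsy text says "Biopsies will be taken according to our center’s common routine" and "The laboratory will stain their own according to local practice". None of these sections names a reader, coded slides, central or independent reading, or masking to arm. Secondary Efficacy Variables lists fibrosis on the 12-month biopsy.

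**Pulse wave velocity.** Contact sensors record over the carotid and femoral arteries. "The PWV will be calculated as the distance between recording sites measured over the surface of the body (L"), divided by the transit time, and the value is averaged over 10 cardiac cycles. What the operator may know about allocation is not addressed.

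**Rank.** Objectives names four important secondary endpoints: graft fibrosis and its markers, GFR, bone density and PWV.

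**The concern.** Giving treatment openly does not require outcomes to be assessed openly. A histological grade involves a reader's judgement, and a PWV measurement depends partly on where the operator places the sensors and how the surface distance is taken. If that person knows who received paricalcitol and expects it to help, borderline calls can lean one way. A lean that differs between arms adds directly to the estimated treatment effect, and a test on the resulting scores cannot tell the two apart.

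Fibrosis carries weight in this protocol. The Introduction singles out its prevention, together with the reduction of proteinuria, as the most interesting prospect of treatment. Proteinuria is protected by automated measurement; the fibrosis grade has no comparable protection in the text.

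Slide labelling and what an operator is told are matters of trial conduct, settled when samples are read and measurements taken. The absence of a statistical analysis plan from the available documents therefore does not explain the silence.

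**Working it through.** **1. Does any text mask an assessor?**

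- Overall Study Design and Randomisation: treatment is open and the list is at the site.
- Kidney biopsy, the protocol-biopsy text and the fibrosis-marker section: no masking is stated.
- Pulse Wave Velocity: no masking is stated.
- Study Populations: the only mention of blindness in the plan outside the reference list is a review meeting that sets per-protocol criteria. It does not concern outcome reading.
- The main hypothesis and Study Populations mention placebo, but Overall Study Design gives controls no treatment, so this wording masks nobody.

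**2. Which outcomes are exposed?**

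| Outcome | How obtained | Exposure |
|---|---|---|
| Albumin/creatinine ratio (primary) | Measured automatically | Not material |
| eGFR | Formula on laboratory values | Not material |
| RNA fibrosis markers | Assay | Small |
| PWV | Device recording over 10 cycles; operator sets sensors and distance | Moderate |
| IF/TA grade | Graded by a reader | Greatest |

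**3. How much could a tilt matter?**

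The plan has no figure to reproduce here: it gives no SD, effect size or power for IF/TA. The 30 per arm in Estimation of Sample Size was derived for albuminuria. It serves below only as a group size, and the masking point does not depend on whether it is correct.

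Inputs:
- n = 30 per arm and a 5% type I error (protocol). Two-sided testing is assumed, since sidedness is not stated.
- Grade SD of 0.7 to 0.9 (assumption).
- Between-arm reader tilt b of 0.1, 0.2 or 0.3 grade (assumption).
- No true effect, and a two-sample t-test on the grade (assumption).

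Formulas: SE = SD × √(2/n); noncentrality = b/SE; the false-positive rate is the probability that a noncentral t with 2n − 2 = 58 degrees of freedom falls outside ±2.002.

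- SD 0.7: SE = 0.7 × √(2/30) = 0.181.
- SD 0.9: SE = 0.9 × √(2/30) = 0.232.

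| Tilt b (grade) | b/SE, SD 0.9 | Rate, SD 0.9 | b/SE, SD 0.7 | Rate, SD 0.7 |
|---|---|---|---|---|
| 0 | 0 | 5.0% | 0 | 5.0% |
| 0.1 | 0.43 | 7.1% | 0.55 | 8.5% |
| 0.2 | 0.86 | 13.5% | 1.11 | 19.3% |
| 0.3 | 1.29 | 24.6% | 1.66 | 37.2% |

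At 35 per arm (the 70 randomised, split 1:1) the ranges are 7.4-9.1%, 15.0-21.8% and 28.0-42.4%. A larger trial makes a fixed tilt more likely to reach significance, not less.

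In SD units with a normal approximation at 30 per arm, a tilt of 0.1, 0.2, 0.3 or 0.5 SD gives 6.7%, 12.1%, 21.3% or 49.1%. This scale needs no assumption about the grade SD.

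**The case against.** The strongest reply is that the risk is inferred from silence. The biopsies are routine for all transplanted patients, nothing says that the arm is sent to pathology, and labelling rules could sit in a laboratory manual. The pathologist may in practice not know the arm. That is fair, and it is why the point is put as a risk. But the protocol does not secure that ignorance, and if it already holds, writing it down costs almost nothing.

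The magnitude also rests on assumed values. It shows what a given tilt would do, not how likely a tilt is. That stands too.

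A reader might infer several stronger things that the documents do not support:

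- *That the main secondary results as a whole are compromised.* eGFR is calculated from laboratory values, RNA expression is assayed, and bone density is described as a standard clinical measurement. The point is confined to IF/TA and PWV.
- *That fibrosis alone is the trial's headline interest.* The Introduction names it alongside proteinuria, and proteinuria is the automated primary.
- *That the damage would be permanent.* Stored slides can be coded and re-read. PWV is the outcome fixed at acquisition.
- *That the reader must also be unaware of the visit.* Knowing baseline from 12 months without knowing the arm does not by itself favour either arm.
- *That the protocol describes grading purely by eye or a distance taken by hand.* These are plausible readings, but the text says Banff criteria plus morphological techniques, and a surface measurement.

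For PWV, masking will be imperfect because patients know their treatment and can mention it.

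**Conclusion.** The point holds for two outcomes. As written, the 12-month IF/TA grade may be read, and PWV measured, by someone who knows the allocation; exposure is clearly greater for IF/TA. The primary analysis is not materially affected, so this is a change that should be made rather than one on which the trial's main conclusion turns.

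The size is conditional. With 30 per arm, a grade SD of 0.7 to 0.9, a two-sided 5% t-test and no true effect, a tilt of 0.1, 0.2 or 0.3 grade takes the false-positive rate to about 7-9%, 14-19% or 25-37%. SD, tilt and test are assumptions, and no comparable figure is offered for PWV. Nothing in the protocol shows that bias has occurred or will occur.

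**What to change.** - **Kidney biopsy and fibrosis-marker sections:** state that the trial IF/TA score is read by the usual pathologist from slides carrying a study code, with no allocation on the slide or the request form.
- **Pulse Wave Velocity section:** state that the operator is not told the arm and that patients are asked not to disclose it.
- **Optional:** mask visit order and code the RNA samples. Neither is needed to protect the between-arm comparison of the grade.

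Treatment stays open, and no extra biopsies, patients or second reader are required. The cost is coded labels and some handling time. Because the clinical report needs the patient's identity, the trial score may have to be read in a separate batch by the same pathologist, who could remember some cases. Masking of PWV will remain incomplete.

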**Protocol biopsies are routinely performed on all transplanted patients at week 6 and month 12.**

Two renal biopsies are mandatory in the study protocol. The first biopsy should be taken at the time of inclusion, the second at 12 months after transplantation, respectively. There will not be required to obtain extra biopsy due to participation in the trial.

Biopsies will be taken according to our center’s common routine.

The Banff standard regarding the presence of sufficient number of glomeruli and arteries will be used

The laboratory will stain their own according to local practice. In addition the slides will be stained for C4d. The routine biopsy for C4d will be utilized for expression of fibrosis markers.

#### Expression of Fibrosis markers in graft biopsies

Graft fibrosis will be assessed by Banff criteria and by morphological techniques.

RNA expression of following fibrosis markers

Transforming growth factor beta (TGF-beta)

Osteopontin

Thrombospondins

Tenascins

Osteonectin/Sparcs

Periostin

#### Clinical laboratory tests - blood

At all visits to the clinic routine laboratory samples are to be taken for the assessment of haematological and clinical chemistry variables.

The following variables will be measured:

Haematology:

[WBC](http://www.labtestsonline.org/understanding/analytes/glucose/glance.html) (white blood cells), [HgB](http://www.labtestsonline.org/understanding/analytes/glucose/glance.html) (haemoglobin), and platelets.

Clinical chemistry:

[Calcium](http://www.labtestsonline.org/understanding/analytes/calcium/glance.html), sodium, potassium, creatinine, AST (aspartate aminotransferase), ALT (alanine aminotransferase), BASP, LD, bilirubin, albumin, blood urea nitrogen (BUN), parathyroid hormone (PTH) and C-reactive protein (CRP).

#### Clinical laboratory tests - urine

Proteinuria will be evaluated with a spot urine for albumin/creatinine. Spot urine will be measured according to standard methods. Urine samples for evaluation of proteinuria will be taken at Baseline and at the Final Safety Follow-up visit.

#### Markers of Bone Turnover and Inflammation status

- PTH-3 generations assay
- 25-vit D
- PINP (N-terminal propeptide of human procollagen type I)
- Osteocalcin
- NTX (cross-linked N-telopeptides of bone type I collagen)
- Fasting blood glucose
- Insulin
- Leptin
- Adiponectin Fetuin A
- BAP (bone specific alkaline phosphatase)
- FGF23
- Calcitonin
- Osteoprotegerin
- Selected biomarkers reflecting inflammatory pathways (to be determined later)
- Body composition (by BMD).

#### Markers of Crystallization inhibitors

Fetuin-A, MGP and FGF-23.

#### Pulse Wave Velocity

1. Arterial stiffness will be assessed by means of PWV measurements using “SphygmoCor™” (Atcor Medical, Sidney, Australia), a non-invasive technique with direct-contact pulse sensors (Covic et al., 2005). Pulse waveforms will be recorded simultaneously, obtained transcutaneously over the common carotid artery and femoral artery in the groin. The PWV will be calculated as the distance between recording sites measured over the surface of the body (L), divided by the time interval (t) between the feet of the flow waves (PWV = L/t). The value is averaged over 10 cardiac cycles (Asmar et al., 1995).

#### Bone Mineral Density

Standard clinical measurements.

#### Glomerular filtration rate estimated by Modification of Diet of Renal Disease (MDDR) formula.

Kidney function is to be evaluated with estimated GFR (eGFR) at the Baseline visit (Visit 2, Day 0) and at the Final Safety Follow-up visit (Visit 4, Week 48).

### Safety evaluation methods

During the course of the trial the investigator will report adverse events. Adverse events including intensity, duration and relation to treatment will be recorded in the Case Report Form (CRF). Adverse events and serious adverse events will be collected from the date of informed consent until 7 days after the last dose of the investigational product. All adverse events will be followed up until resolved or as clinically required. For details about adverse event reporting, please see Section 6.3, below.

Safety data will be monitored throughout the study and regularly reviewed by an independent Data Monitoring Committee (DMC).

## Scheduling of Procedures

### Screening

- Informed consent
- Inclusion/exclusion criteria review
- Medical history and concomitant diseases
- Concomitant medication
- Physical examination
- Vital signs

### Visit 1, Baseline (Day 0) (week 6 after transplantation)

- Review of eligibility criteria
- Review of medical history and concomitant diseases
- Concomitant medication
- Physical examination
- Vital signs
- Randomisation
- Study drug administration
- Estimated GFR
- Kidney biopsy
- Clinical laboratory tests
- Urine samples
- Markers of bone turnover
- Endothelial- and inflammatory markers
- Echocardiography
- Pulse wave velocity
- Bone mineral density
- Adverse events

### Visits 3a-3c, Initial Safety Follow-up (Week 2, 4 and 6)

- Concomitant medication
- Clinical laboratory tests
- Adverse events

### Visit 10, Final Safety Follow-up (Week 48)

- Concomitant medication
- Physical examination
- Vital signs
- Clinical laboratory tests
- Urine samples
- Markers of bone turnover
- Endothelial- and inflammatory markers
- CD19
- Immunoglobulins
- DSA
- Estimated GFR
- Kidney biopsy
- Adverse events

# STUDY MEDICATION

## Study Medication and Comparator

Patients are randomized into two arms. Paricalcitol will be prescribed for the active arm.

## Dosage and Administration

### *Paricalcitol Titration*

The dose for paricalcitol will be 2 μg/day. The data monitoring committee will monitor levels of Ca, P and PTH. The dose of paricalcitol should be reduced with 50% if s-calcium exceeds 2.75 (11 mg/dl) at 2 consecutive measurements.

## Duration of Treatment

Patient will be receiving treatment for 48 months after randomization.

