## Statistical Analysis Plan

The main hypothesis:

In renal transplant recipients’ treatment with paricalcitol is superior to placebo, and results in reduced albuminuria at 12 months treatment.

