## End of Trial

The end of the trial is defined as the last visit of the last patient included in the trial. The Competent Authorities and the Ethics Committees, as applicable, will be notified about the end of the trial.

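### Duration of Treatment sets paricalcitol at 48 months, while the visits, flow chart, treatment phase and hypothesis all end at Week 48 or 12 months

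*Protocol*

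**What the plan says.** The whole of Duration of Treatment is one sentence: "Patient will be receiving treatment for 48 months after randomization".

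The rest of the protocol places the end of treatment and of study participation about one year after randomisation:

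- Overall Study Design: "At Week 48 of the study, the patient will return to the clinic for the final Final Follow-up visit (Visit 12, Week 48"). The schedule of procedures gives the same week under "Visit 10, Final Safety Follow-up (Week 48"). Clinic visits, Proteinuria and the section on estimated GFR also name Week 48. The visit number varies (12, 10 or 4), but the week does not.
- Study drug administration: "Patients allocated to Paricalcitol will get a prescription of orally 2 ug once daily for the entire duration of the study". This ties dosing to the length of the study.
- Proteinuria: "Measured as albumin/creatinine ratio at baseline and after 12 months".
- Statistical Analysis Plan: the hypothesis is that treatment "results in reduced albuminuria at 12 months treatment".
- Study Populations: per-protocol patients are those who finish the treatment phase at 12 months.
- Patient Treatment Plan: on completing the study, each patient goes back to the standard treatment received before it.
- Study flow chart: the last column is month 12, and it includes drug return and accountability.

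Two further rules depend on when dosing stops. Safety evaluation methods collects adverse events until seven days past the final dose. End of Trial reads: "The end of the trial is defined as the last visit of the last patient included in the trial".

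**The concern.** Duration of Treatment is where a site, a pharmacy or an ethics committee would look up how long the drug is given, and it is the section that states a figure under that heading. That figure conflicts with everything the protocol schedules.

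What is at stake is exposure and its monitoring. A site that follows this sentence keeps patients on drug for about three years beyond the last planned visit. A site that follows the schedule stops at the final visit. Under the longer reading, the calcium-triggered dose reduction in Paricalcitol Titration, which needs two consecutive measurements, would have no scheduled values to act on once the final visit has passed.

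**Working it through.** No formula in the protocol produces the 48-month figure, so the check is a unit conversion and a comparison of the texts.

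Inputs: 48 months (Duration of Treatment); Week 48 (Overall Study Design and the schedule of procedures); 12 months (Proteinuria, Statistical Analysis Plan, Study Populations, flow chart).

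1. Weeks per month: 365.25 / 7 / 12 = 4.348.
2. Stated treatment length: 48 × 4.348 = 208.7 weeks.
3. Ratio to the final visit: 208.7 / 48 = 4.35, about 4.3-fold. Against 12 months: 48 / 12 = 4-fold.
4. Exposure after the final visit: 208.7 − 48 = 160.7, about 161 weeks, or 160.7 / 4.348 = 37 months. Counted from month 12 instead: 48 − 12 = 36 months.
5. Agreement of the other two figures: 48 weeks = 48 / 4.348 = 11.0 months, and 12 months = 12 × 4.348 = 52.2 weeks. They lie about four weeks apart and describe the same one-year study. Neither is near 48 months.

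The literal reading can then be followed through the dependent rules:

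- Visits, laboratory tests and accountability: neither the schedule of procedures nor the flow chart has an entry after Week 48 or month 12. The 161 weeks contain none.
- Adverse events: the window closes seven days after the last dose, so it would run to 48 months plus 7 days. The patient's last visit would already have taken place at Week 48.
- End of trial: this is the last patient's last visit, at that patient's Week 48. For that patient the adverse-event window would stay open for about 161 weeks plus 7 days after the trial had ended. For patients randomised earlier, the overrun depends on the length of recruitment, which the protocol does not state.

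The sample-size paragraph uses a difference of 5.2 mg/mmol, a baseline of 15.0 with a spread of 10, a correlation of 0.5 and the two error rates. It has no duration input, so nothing there changes.

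**The case against.** The strongest reply is that this is one stray sentence, possibly a slip of unit, set against many statements that agree with each other. A site would have to overlook the 12-month treatment phase, the return to earlier treatment at study completion and the drug return at the last flow-chart visit in order to go on dosing. This largely stands: the protocol does not describe two rival designs. It does not remove the problem, because the sentence is current text under the heading that governs duration. The flow chart is not wholly clean either, since it marks drug dispensation as well as return in its last column.

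A reader might also infer more than the documents support:

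- That adverse-event collection stops at the final visit. It does not, because the window follows the last dose and would lengthen with treatment. What is missing is any scheduled visit to support it. The data monitoring committee's review would continue in principle, but without scheduled measurements.
- That phosphate checks cease at Week 48. Phosphate is not in the listed clinical chemistry panel at any visit.
- That efficacy follow-up or the per-protocol set is left undefined. Follow-up is consistently about one year, and the per-protocol definition names 12 months.
- That drug supply would be wrong by a known amount. The protocol states no supply quantity.
- That this is the only text on treatment length. Study drug administration, Study Populations and the hypothesis also bear on it.

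Routine care might still measure calcium after the final visit, but the protocol neither schedules nor collects those values.

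**Conclusion.** The contradiction is real and should be corrected. As written, Duration of Treatment implies about 209 weeks of drug against a 48-week study. That is a 4.3-fold difference and leaves about 161 weeks of exposure with no scheduled visit, laboratory test or accountability. It also carries the adverse-event window past each patient's last visit and, with certainty for the last patient included, past the end of trial. These sizes rest only on reading the sentence literally and on an average month of 4.348 weeks.

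The consequence concerns exposure and safety monitoring. The primary comparison, its time point, the per-protocol definition and the sample size stay as they are. The four-week gap between 48 weeks and 12 months is a separate, minor matter and adds no weight here.

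**What to change.** Amend Duration of Treatment so that it agrees with Overall Study Design, Study drug administration, Proteinuria, Safety evaluation methods, the Week 48 visit in the schedule of procedures, Statistical Analysis Plan, Study Populations, Patient Treatment Plan, End of Trial and the flow chart. One treatment duration and one end-of-treatment visit should apply throughout. The sponsor must confirm which duration is intended; this review does not choose between them.

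The cost is a one-line change by amendment, with a check that the patient information, which is not among the documents reviewed, gives the same duration. No analysis or sample-size work is needed.
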